### Sample size

Sample size calculation was performed with G*Power 3.1 [30], using *F* test between factors with two groups (intervention and placebo) and three evaluation sessions (before administration, after administration, 12 and 24 weeks after administration). Since there was no pre-experiment before, we chose to take the average effect as 0.25, an *α* error probability of 0.05, and a power (1-β error probability) of 0.80. We take the Corr among rep measures as 0; the Nonsphericition correction ɛ is 1/(4–1) ≈ 1.34; the resulting total sample size is 95, because it has to be repeated 4 times; and the final sample size of each group is 24. Allowing for a maximum dropout rate of 30%, the number of subjects in the treatment group has been set to 30 participants. Based on the needs of our project, it is proposed to recruit high PM2.5 exposure and low PM2.5 exposure groups, and the groups are divided into intervention and placebo groups, according to each group requires a sample size of 30 patients, for a total of 120 patients.

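### The sample size divides a participant total of 95 by the 4 visits to reach 24 per group; on the inputs that reproduce 95, 24 versus 24 has about 50% power, not 80%

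*Protocol article*

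**What the plan says.** All of the inputs are in the Sample size section of the protocol article. The calculation is described as an F "test between factors with two groups (intervention and placebo) and three evaluation sessions", but the sessions then listed are four: "before administration, after administration, 12 and 24 weeks after administration". For the effect size, "we chose to take the average effect as 0.25". Alpha is 0.05, power is 0.80 and the correlation among repeated measures is 0. On sphericity the text reads "the Nonsphericition correction ɛ is 1/(4–1) ≈ 1.34".

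The result is given as "the resulting total sample size is 95, because it has to be repeated 4 times", followed by 24 per group. This is raised to 30 to allow for up to 30% dropout. Thirty is then applied to each of four cells (high or low exposure, probiotic or placebo), for 120 in all. The sections on randomization and treatment regimen confirm 30 versus 30 within each exposure stratum. Statistical methods plans a repeated-measures ANOVA of time and time-by-group effects.

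**The concern.** The only reason given for going from 95 to 24 is that each participant is measured four times. That treats 95 as a count of observations. In a G*Power repeated-measures calculation the total is a count of participants, each measured at every visit, and the number of visits is an input. If 95 is a participant total, the two named groups need about 48 each, and a 24-versus-24 comparison has well below the claimed 80% power.

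This paragraph is the article's only justification for the sample size. It presents 30 per arm as sufficient within each exposure stratum, and the title places the question in the high-exposure population. A reader of a null result there could take it as coming from an 80%-powered comparison.

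The stated inputs also disagree with each other: the named test, the epsilon value, the number of sessions and the dropout allowance.

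**Working it through.** **Inputs, all from Sample size:** f = 0.25, alpha = 0.05, target power 0.80, k = 2 groups, correlation rho = 0. I take m = 4 visits, because four are listed and epsilon is written with 4−1. Epsilon is printed as 1.34, but 1/(4−1) = 0.333 and epsilon cannot exceed 1. I assume 0.34 was meant and use the range 0.333 to 0.34.

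**Step 1: reproduce 95.** For the time-by-group test, use the noncentral F distribution with
- lambda = f² × N × m × eps / (1 − rho)
- df1 = (k−1)(m−1) × eps
- df2 = (N−k)(m−1) × eps

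With eps = 0.34 and N = 95: lambda = 0.0625 × 95 × 4 × 0.34 = 8.075, df1 = 1.02, df2 = 93 × 1.02 = 94.86, power 0.801. N = 94 gives 0.796, so 95 is the smallest N that reaches 80%. With eps = 1/3 the answer is 97. With two groups the within-factor (time) test has the same lambda and degrees of freedom, so it also gives 95.

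**Step 2: try the other readings.**

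| Reading (f = 0.25, rho = 0) | Total N for 80% |
|---|---|
| Between factors, m = 4 | 34 |
| Between factors, m = 3 | 44 |
| Time-by-group, m = 4, eps = 1 | 45 |
| Time-by-group, m = 4, eps = 1.34 as printed | 37 |
| One-way, two groups, single measurement | 128 |

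None of these gives 95. For between factors, lambda = f² × N × m / (1 + (m−1) × rho) with df 1 and N−2. At N = 34, lambda = 8.5 and power is 0.807; at N = 33 power is 0.795.

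**Step 3: what the division does.** 95/4 = 23.75, rounded to 24. But m = 4 is already inside lambda. For two groups the split is 95/2 = 47.5, about 48 per group.

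**Step 4: power of the sizes used, in the calculation that yields 95.**

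| Comparison | N | eps = 1/3 | eps = 0.34 |
|---|---|---|---|
| 24 v 24 | 48 | 0.499 | 0.504 |
| 30 v 30, no dropout | 60 | 0.594 | 0.600 |
| 30 v 30 after 30% dropout (60 × 0.70) | 42 | 0.447 | 0.451 |
| Pooled 60 v 60, no dropout | 120 | 0.880 | 0.885 |
| Pooled after 30% dropout (120 × 0.70) | 84 | 0.744 | 0.750 |

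**Step 5: sensitivity at N = 48.** The correlation of 0.5 is my assumption; the article states 0.
- Between factors, rho = 0: lambda = 0.0625 × 48 × 4 = 12, power 0.92.
- Between factors, rho = 0.5: lambda = 12/2.5 = 4.8, power 0.57.
- Time-by-group, rho = 0.5, eps = 1/3: lambda = 4/0.5 = 8, power 0.79.
- Time-by-group, rho = 0, eps = 1: power 0.83.

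**Step 6: dropout.** 24/(1 − 0.30) = 34.3, so 35 per group. Thirty per group covers 1 − 24/30 = 20% dropout.

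**The case against.** The strongest reply is that 50% is not a property of the design. It needs the time-by-group test, correlation 0 and the lowest possible epsilon together. Step 5 gives a range of about 50% to 92% at 48 participants, and the top of it belongs to the very test the section names, at its own correlation of 0. This stands. A reader might infer that the trial is shown to have 50% power; the article does not support that without conditions. It supports something narrower: the stated 80% and the total of 95 come from one calculation, and in that calculation 24 versus 24 has 50%. The favourable 92% cannot rescue the paragraph, because that test does not lead to 95.

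Second, the source of 95 is inferred. It fits a pure time effect as well as time-by-group, and a within-factor test with four groups also gives 95 at epsilon 0.34. Since 95/4 is about 24 per cell in a four-cell trial, the division might be right with a garbled reason. This cannot be excluded, but the text says two groups and gives the repeats as the reason. A within-factor test also concerns change over time, not probiotic against placebo. A four-group time-by-group test would need 134.

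Third, pooling the strata restores power: 96 completers have about 80% and all 120 about 88%. That is correct, and no section says that the probiotic test is run only within strata. Equally, none names the pooled comparison as the powered one, and Sample size treats 30 as what each cell requires. After the planned 30% dropout the pooled figure is about 75%.

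**Conclusion.** The point holds in conditional form. Dividing a participant total of 95 by the number of visits is an error, and for the two groups named 95 means about 48 each. On the inputs that reproduce 95 (f = 0.25, 4 visits, correlation 0, epsilon about 0.34, time-by-group or within-factor test), power is about 50% for 24 versus 24, about 60% for 30 versus 30, and about 45% with 42 completers, against the stated 80%.

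The result rests on reading the printed epsilon as 0.34 and, for the comparison of arms, on taking time-by-group as the intended test because Statistical methods plans it. Under the named between-factors test at correlation 0, 48 participants would be more than enough, but that test needs 34 and not 95. On any reading tried, the paragraph does not agree with itself. It would be too strong to conclude that the trial as a whole is underpowered: pooled over strata, 120 participants have about 88% on the same inputs.

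**What to change.** Rewrite the Sample size paragraph as follows.

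- Remove the division by 4 and state that 95 is the total number of participants.
- State 4 visits, not three, and epsilon of about 0.33, not 1.34. At exactly 1/3 the total is 97.
- Name the test intended. If it is the time-by-group effect in Statistical methods, say so and drop the between-factors label.
- Correct the dropout step: 24 inflated for 30% is 35, and 30 covers only 20%.
- Keep 120 enrolled and restate power on the plan's own inputs: about 60% (45% after 30% dropout) for probiotic versus placebo within one exposure stratum, and about 88% (75% after 30% dropout) pooled over strata.
- Say which of these comparisons the 80% claim refers to. This is a decision about the trial's question and belongs to the investigators; it is more than an edit of wording.

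The cost is one rewritten paragraph and that decision. No extra participants are needed, but the stated power for the high-exposure stratum becomes less favourable.

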### Treatment regimen

According to the working environment and the PM2.5 concentration of the working environment, the participants will be automatically divided into two groups: PM2.5 high-exposure group and PM2.5 low-exposure group. We will recruit a total of 120 participants, including 60 in the high-exposure group and 60 in the low-exposure group. Of the 60 participants in the high-exposure group, 30 will be given probiotics and another 30 will be given placebos. The same is true of 60 participants in the low-exposure group of PM2.5, who will be assigned 30 participants to take probiotics and another 30 to receive a placebo.

1. Intervention group: The intervention group will get probiotics. The same batch of Culturelle capsules provided by American i-Health (Cromwell, CT, USA) will be swallowed with warm water at < 36 °C, one tablet at a time, once per day, over the test period of 4 weeks. The follow-up period will be 24 weeks. As our drugs are live probiotics, in order to maintain better efficacy, we will advise patients to put our medicine in the 4 °C refrigerator.

2. Placebo group: The placebo group will get placebos, the same batch of placebo made by placebo Experimental Center, School of Pharmacy, Chengdu University of TCM. The placebo is made of starch without any efficacy or side effects and also will be swallowed with warm water at < 36 °C, one tablet at a time, once per day, over the test period of 4 weeks. The follow-up period will be 24 weeks. All drugs will be stored in a 4 °C refrigerator.

3. The intervention group and placebo group capsules will be packaged with the same label, each box containing a 4-week dose, a clearly visible label on each package stating “trial only”, and other information including name, dose, administration schedule, storage condition indication, expiration date, and manufacturer name. The reception, handling, storage, and distribution of drugs will be the responsibility of [name], a pharmacist. In this subject, we chose placebo as the comparator. Because it is a kind of “simulated” drug, its physical properties such as appearance, size, color, dosage form, weight, taste, and smell are the same as those of the experimental drug, but it does not contain the active ingredients of the experimental drug and can reflect the “absolute” efficacy and safety of the tested drugs.

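### Thirty per group covers 20% dropout, not the stated 30%: keeping 24 after a 30% loss needs 35, and 30 enrolled would leave 21

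*Protocol article*

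**What the plan says.** The Sample size section takes a total of 95 from G*Power, divides it by four and concludes that "the final sample size of each group is 24". It then applies the dropout allowance: "Allowing for a maximum dropout rate of 30%, the number of subjects in the treatment group has been set to 30 participants". The same figure is carried over the four combinations of exposure (high, low) and treatment (probiotic, placebo): "according to each group requires a sample size of 30 patients, for a total of 120 patients".

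The rest of the article uses the same numbers. Treatment regimen states "Of the 60 participants in the high-exposure group, 30 will be given probiotics and another 30 will be given placebos" and the same split for the low-exposure group. Participant recruitment and Randomization and allocation concealment both repeat 120, and the latter gives 60 per exposure group. No other section gives a different dropout rate or another way of allowing for dropout.

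**The concern.** A dropout allowance links three numbers: those needed for analysis, those enrolled, and the fraction expected to be lost. Any two of them fix the third. Here all three are stated, and 24, 30% and 30 cannot hold together.

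The error is in the unfavourable direction, since the article claims more protection against loss than the enrolled number gives. A reader would take it that the trial can lose three participants in ten from each group and still have the planned number. At that loss, every one of the four groups falls below the plan's own requirement. Follow-up runs to 24 weeks after the final treatment and the size calculation counts four measurement times, so the allowance is a working part of this design.

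**Working it through.** **Inputs, all from the Sample size section**

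- Required per group: 24 ("the final sample size of each group is 24")
- Dropout: 30%, given as a maximum
- Enrolled per group: 30, in four groups, 120 in total
- For power: effect size f = 0.25 ("we chose to take the average effect as 0.25"), α = 0.05, target power 0.80, two groups, four measurements, correlation 0 between repeated measures

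**Step 1. The plan's 24.** The article says "the resulting total sample size is 95, because it has to be repeated 4 times". 95/4 = 23.75, rounded up to 24. So 24 follows from the article's own division. Whether that division is valid is a separate question.

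**Step 2. The dropout step.** With required number n and dropout fraction d, the number to enrol is n/(1 − d).

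| Rule | Calculation | Per group |
|---|---|---|
| Correct inflation | 24/(1 − 0.30) = 34.29 | 35 (140 in total) |
| Correct, from the unrounded figure | 23.75/0.70 = 33.93 | 34 |
| Common shortcut n(1 + d), which is too small | 24 × 1.30 = 31.2 | 32 |
| Shortcut, from the unrounded figure | 23.75 × 1.30 = 30.9 | 31 |
| Stated in the plan | | 30 (120 in total) |

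Inflating the undivided total gives 95/0.70 = 135.7, so 136, again not 120. None of these rules gives 30. The shortcut comes closest, but it is not a valid rule: 32 enrolled would leave 32 × 0.70 = 22.4.

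**Step 3. What 30 per group does cover.** The largest tolerable loss is 1 − 24/30 = 0.20. Equivalently, 24/0.80 = 30 exactly.

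**Step 4. What remains at 30% dropout.** 30 × 0.70 = 21 per group, a shortfall of 3 in 24 (12.5%). Over four groups, 4 × 21 = 84, against the calculated 95.

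**Step 5. Effect on power.** The article's description of the power calculation does not define one model. It names a between-factors F test, speaks of three sessions while listing four, and prints the nonsphericity correction ε as 1/(4−1) ≈ 1.34, although 1/3 is about 0.33. I therefore looked for the reading that returns 95. The within or within-between F test does so, with four measurements and ε = 0.34:

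- λ = f² × N × m × ε/(1 − ρ) = 0.0625 × 95 × 4 × 0.34 = 8.075
- df₁ = (m − 1)ε = 3 × 0.34 = 1.02
- df₂ = (N − 2)(m − 1)ε = 93 × 3 × 0.34 = 94.86
- power = 0.801

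With ε = 1/3 the required total is 97. On this reading:

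| Evaluable | Situation | Power (ε = 1/3 to 0.34) |
|---|---|---|
| 95 | plan's calculated total | 0.795–0.801 |
| 84 | all four groups, 30% dropout | 0.744–0.750 |
| 60 | one exposure stratum, no dropout | 0.594–0.600 |
| 48 | one stratum, 24 per group | 0.499–0.504 |
| 42 | one stratum, 30% dropout | 0.447–0.451 |

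The shortfall against the plan's 24 per group therefore costs about 5 percentage points: from about 0.80 to 0.75 pooled, and from about 0.50 to 0.45 within one stratum. The remaining gap between 0.50 and 0.80 within a stratum comes from dividing 95 by four, not from the dropout figure.

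**The case against.** Four points can be made for the plan.

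*The consequence is small, and much of the low power within a stratum has another cause.* This is right about attribution. Only about 5 points belong to the dropout figure, and the 0.45 within a stratum should not be quoted without the 0.50 that applies when 24 per group is fully reached.

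*The power figures depend on a reconstruction.* Also right. Under the between-factors test that the section names, with four measurements and correlation 0, power would be about 0.99 at 84 and 0.89 at 42. That test does not reproduce 95, however; it needs only 34 in total. The power loss is therefore conditional on the reading chosen. The relation between 24, 30 and 21 does not depend on any test.

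*Thirty per cent is a maximum, and loss may be lower at the primary endpoint.* Outcome measures places the primary endpoint at T1, well before the last visit, so fewer may have dropped out by then. But an allowance for a maximum has to hold at that maximum, and the calculation is built on four measurements, the later visits included.

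*Dropouts are not automatically lost to analysis.* Data management and monitoring foresees carry-forward methods for missing values. They fill cells in the data set but do not restore the missing information, and the allowance in the Sample size section is presented as protection against the loss itself.

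None of this makes the sentence correct.

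**Conclusion.** The concern holds. From the article's own figures, 30 per group allows for 20% dropout, not 30%. A 30% loss leaves 21 of the required 24 in each group (12.5% short) and 84 of 120 overall. A true 30% allowance on 24 would need 35 per group.

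This takes 24 as the number to be evaluated and the dropout rate as equal across groups. The power consequence, about 0.75 instead of 0.80 pooled, further assumes the within or within-between F test with ε between 1/3 and 0.34, which is the reading that yields 95. The effect on power is moderate, but the misstatement is certain, applies to all four groups and makes the design look more robust than it is. It should be corrected.

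**What to change.** Keep 120 enrolled and correct the sentence in one of two ways:

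- state that 30 per group allows for up to 20% dropout, leaving 24 of 30; or
- keep 30% as the maximum and report the power with 21 evaluable per group (84 in total), naming the F test, the value of ε, and whether the comparison pools the exposure strata or is made within one.

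The second is the more informative. The first repeats 24 as an adequate target, so it should be used only once the division of 95 by four has been re-examined. If the base number changes, the dropout step has to be redone as n/(1 − d).

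The cost is one rewritten sentence and, for the second option, one power calculation. No extra recruitment and no change to the design or analysis is needed. The price is a less favourable figure: either a lower tolerance or a lower power.

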### Selection criteria

#### Inclusion criteria for high-exposure population

We intend to include patients aged 22–65 with the following characteristics:
Male and female sanitation workers or traffic polices working in an environment with traffic pollution in Chengdu, for ≥ 3 years, and fixed working time ≥ 8 hNo history of gastroenteritis in the past monthNo hormones or antibiotics were used for a period of 3 months before entering the studyNo nasal spray or other probiotics (such as lactic acid bacteria, Bifidobacterium), yoghurt, or beverage used in the last 1 monthNo lymph node enlargement, inflammation, polyps, mass, runny nose, etc., after clinical examination of lips, throat, ears, nostrils, and neck (especially anterior nostril)No clinically important GI condition (e.g., inflammatory bowel disease, irritable bowel syndrome, gastric reflux, indigestion, dyspepsia, celiac disease, history of surgery for weight loss, gastroparesis, and clinically significant lactose and gluten intolerance or allergies) [31, 32]No recent (within 2 weeks of visit 1; week − 1) history of an episode of acute GI illness such as nausea/vomiting or diarrhea (defined as ≥ 3 loose or liquid stools/day) [31, 32]

#### Inclusion criteria for low-exposure population

We intend to include patients aged 22–65 with the following characteristics:
Male and female staff of Chengdu Urban Environmental Hygiene Administration Bureau and Chengdu Traffic Administration Bureau, working indoors (with air conditioning), for ≥ 3 years, and working time ≥ 8 hNo history of gastroenteritis in the past monthNo hormones or antibiotics were used for a period of 3 months before entering the studyNo nasal spray or other probiotics (such as lactic acid bacteria, Bifidobacterium, etc.), yoghurt, or beverage used in the last one months;No lymph node enlargement, inflammation, polyps, mass, runny nose, etc., after clinical examination of lips, throat, ears, nostrils, and neck (especially anterior nostril)No clinically important GI condition (e.g., inflammatory bowel disease, irritable bowel syndrome, gastric reflux, indigestion, dyspepsia, celiac disease, history of surgery for weight loss, gastroparesis, and clinically significant lactose and gluten intolerance or allergies) [31, 32]No recent (within 2 weeks of visit 1; week − 1) history of an episode of acute GI illness such as nausea/vomiting or diarrhea (defined as ≥ 3 loose or liquid stools/day) [31, 32]

### Exclusion criteria

#### Criteria of excluded participants

History of gastrointestinal surgeryLong history of drug useHistory of smokingPregnancy and lactationCould not understand and cooperate with the experimental processParticipated in other clinical trials within the past month

### Blinding

During the course of the experiment, neither the participants nor the researchers will have the grouping information. The participants will be divided into a placebo group and an intervention group. According to the stratification of high and low exposures, the drug number, label, and packaging for each subject will be compiled from 001 to 060, respectively. The random numbers will be sealed in double opaque envelopes and managed by the researcher ([name]) in charge of the blinding method. Each subject will be equipped with a corresponding emergency letter, and the serial and drug number on the cover and stationery will be confirmed consistent with the label on the drug package. The test name, subject serial number, the group that corresponds with the test, and the specific drugs used will be indicated in the letter. In case serious adverse events occur during the medical process, the envelope will be opened to break the blinding in an emergency and should be kept in reserve by the researcher.

### Treatment regimen

According to the working environment and the PM2.5 concentration of the working environment, the participants will be automatically divided into two groups: PM2.5 high-exposure group and PM2.5 low-exposure group. We will recruit a total of 120 participants, including 60 in the high-exposure group and 60 in the low-exposure group. Of the 60 participants in the high-exposure group, 30 will be given probiotics and another 30 will be given placebos. The same is true of 60 participants in the low-exposure group of PM2.5, who will be assigned 30 participants to take probiotics and another 30 to receive a placebo.

1. Intervention group: The intervention group will get probiotics. The same batch of Culturelle capsules provided by American i-Health (Cromwell, CT, USA) will be swallowed with warm water at < 36 °C, one tablet at a time, once per day, over the test period of 4 weeks. The follow-up period will be 24 weeks. As our drugs are live probiotics, in order to maintain better efficacy, we will advise patients to put our medicine in the 4 °C refrigerator.

2. Placebo group: The placebo group will get placebos, the same batch of placebo made by placebo Experimental Center, School of Pharmacy, Chengdu University of TCM. The placebo is made of starch without any efficacy or side effects and also will be swallowed with warm water at < 36 °C, one tablet at a time, once per day, over the test period of 4 weeks. The follow-up period will be 24 weeks. All drugs will be stored in a 4 °C refrigerator.

3. The intervention group and placebo group capsules will be packaged with the same label, each box containing a 4-week dose, a clearly visible label on each package stating “trial only”, and other information including name, dose, administration schedule, storage condition indication, expiration date, and manufacturer name. The reception, handling, storage, and distribution of drugs will be the responsibility of [name], a pharmacist. In this subject, we chose placebo as the comparator. Because it is a kind of “simulated” drug, its physical properties such as appearance, size, color, dosage form, weight, taste, and smell are the same as those of the experimental drug, but it does not contain the active ingredients of the experimental drug and can reflect the “absolute” efficacy and safety of the tested drugs.

4. If the patient strongly requests to quit, the trial can be suspended. The drug in this project is a dietary supplement with controllable safety risks and no definite adverse reactions for the time being. However, if the patient has diarrhea or nausea, the trial can be suspended and adverse events can be reported. This project mainly observed the intestinal and nasal microbiota of the participants. Therefore, drugs that interfere with the microbiota, such as antibiotics and other probiotics, are prohibited, while implementing for the treatment of other diseases will not require alteration and continue for both trial arms.

